#### Secondary Outcome Analysis

Linear mixed effects models will be used to analyze continuous variables with repeated measures (eg, scale scores at multiple time points). The models will include group, time, and their interaction as fixed effects; individual subject IDs and study centers will be incorporated as random effects.

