### Eligibility Criteria

#### Inclusion Criteria

The inclusion criteria are as follows:

Histologically or cytologically confirmed primary epithelial ovarian cancer.Meeting the diagnostic criteria for chronic insomnia defined by the Sleep Disorders Group of the Neurology Branch of the Chinese Medical Association, including a Pittsburgh Sleep Quality Index total score >8, a Piper Fatigue Scale total score >4, and a Patient Health Questionnaire-9 total score >5.Moderate-to-severe PNSC severity. PNSC will be assessed using the MDASI-OC. Moderate-to-severe PNSC is defined as a mean score of ≥4 across the 4 items: sleep disturbance, fatigue, distress, and sadness.Eastern Cooperative Oncology Group Performance Status score of 0 to 2.Age 18 to 70 years.Meeting the TCM diagnostic criteria for spleen-kidney yang deficiency syndrome.Expected survival >1 year.Signed informed consent form with voluntary acceptance of the treatment protocol and ability to independently complete sleep diaries.

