### Outcomes

#### Primary Outcome

The PNSC score is constructed based on the 4 most relevant symptoms (fatigue, sleep disturbance, distress, and sadness) from the MDASI-OC scale, in accordance with its usage guidelines [24]. Each symptom is rated on an 11-point scale, ranging from 0 (“no symptom”) to 10 (“the most severe imaginable”). The primary efficacy end point of this study is the difference in the PNSC remission rates between the intervention and control groups at 3 months after enrollment. Given that there is no universally accepted evaluation standard for the remission of this specific cluster, “remission” is defined in this protocol through expert consensus. A participant is classified as in “remission” if they meet at least one of the following PNSC-specific criteria: a ≥50% reduction in the total PNSC score relative to the baseline or an absolute PNSC score falling below the threshold of 4 after the intervention. While the primary comparison between the 2 groups will focus on the 3-month mark, longitudinal assessments will be conducted at baseline and at 1, 2, 3, 6, 9, and 12 months after enrollment to monitor symptom dynamics.

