#### Primary Outcome Analysis

The primary end point is the PNSC remission rate at 3 months after enrollment. The chi-square test will be used to analyze whether the difference in remission rates between the two groups is statistically significant. Meanwhile, the difference in remission rates between the experimental group and the control group, along with the 95% CI, will be calculated. In addition, to account for potential between-group heterogeneity, a binary logistic regression model will be performed, with group as the main independent variable and baseline PNSC scores included as covariates. Study center will be included as a fixed effect to account for potential between-center heterogeneity. In addition, longitudinal PNSC scores will be analyzed using the methods described below for repeated continuous outcomes.

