#### Survival Outcomes

One-year OS and PFS will be analyzed using the Kaplan-Meier method with log-rank tests. A Cox proportional hazards model will be used to estimate hazard ratios.

A one-sided *P* value of <.03 will be considered statistically significant.

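### As ordinarily read, the mixed model for repeated scores assumes constant variance and correlation over seven visits and omits baseline adjustment: this loses month-3 power and can mis-size change-from-baseline tests

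*Protocol article*

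**What the plan says.** Secondary Outcome Analysis gives one model for all repeated continuous outcomes: "Linear mixed effects models will be used to analyze continuous variables with repeated measures (eg, scale scores at multiple time points"). Its terms are then listed: "The models will include group, time, and their interaction as fixed effects; individual subject IDs and study centers will be incorporated as random effects". There is no baseline covariate. The section does not say whether time is categorical or continuous, which residual covariance applies, or which contrast is the treatment effect.

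Primary Outcome Analysis extends the same model to the symptom-cluster score: "longitudinal PNSC scores will be analyzed using the methods described below for repeated continuous outcomes". The same section includes the baseline PNSC score as a covariate in the logistic model for remission. The primary test itself is separate: "The chi-square test will be used to analyze whether the difference in remission rates between the two groups is statistically significant".

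The visits are unequally spaced: "longitudinal assessments will be conducted at baseline and at 1, 2, 3, 6, 9, and 12 months after enrollment to monitor symptom dynamics". Treatment lasts 3 months, so the last three visits are off treatment. Inclusion Criteria restrict the baseline scores, for example "Moderate-to-severe PNSC is defined as a mean score of ≥4 across the 4 items: sleep disturbance, fatigue, distress, and sadness".

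**The concern.** A subject random intercept implies that scores one month apart are as strongly correlated as scores twelve months apart, and that the variance is the same at every visit. Both are doubtful here.

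- **Correlation.** Symptom scores of patients on changing cancer treatment are likely to be more alike at adjacent visits than a year apart.
- **Variance.** Eligibility narrows the baseline distribution. Inclusion requires PHQ-9 above 5 and exclusion removes 15 or more, so baseline PHQ-9 lies between 6 and 14. Later scores can span 0 to 27. PSQI, Piper and PNSC also have a lower cut, and GAD-7 an upper one. Baseline is one of the modelled visits.

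With baseline as an outcome and a free group effect at baseline, the model also does not use the baseline score to reduce the residual variance of the later comparison. The logistic model does use it.

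At stake are the results for PSQI, PHQ-9, GAD-7, Piper, EORTC, the TCM scale and the continuous PNSC score. The risks are lost power at the end of treatment and, if late change-from-baseline contrasts are tested, too many false claims of lasting benefit.

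**Working it through.** **The plan's own figure.** No sample size, power or error rate is stated for the mixed model. The stated size belongs to the binary endpoint and reproduces: (1.960 + 0.842)² × (0.10×0.90 + 0.40×0.60) / (0.30 − 0.15)² = 115.1, so 116 per group, and 116/0.8 = 145. It does not depend on the model examined here.

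**Inputs.** From the documents: seven visits, and 158 per arm less 20% dropout (158 × 0.8 ≈ 126). One-sided 0.025 is taken from Sample Size. Assumed, because the documents give no correlations or SDs: unit variance at each visit; correlation between visits t months apart of 0.85 × [s + (1 − s) × d^t], with stable part s = 0 or 0.5, decay d = 0.8 or 0.9, and 15% noise; a true month-3 effect of 0.30 SD. Center is left out.

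**Formulas (large sample).** Let v and c be the average variance and average covariance over the seven visits. In units of 2/n:

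- The random-intercept model takes the variance of any change contrast as 2(v − c).
- The true variance of the change to visit k is V00 + Vkk − 2V0k.
- Actual one-sided size = 1 − Φ(1.960 × √[model variance / true variance]).
- With baseline adjustment the variance at visit k is Vkk(1 − ρ²), where ρ is the correlation with baseline.

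**Worked case, s = 0, d = 0.9.** The average of 0.9^t over visit pairs is 0.605, so c = 0.85 × 0.605 = 0.514 and the model variance is 2(1 − 0.514) = 0.971.

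- Month 3: ρ = 0.85 × 0.9³ = 0.620; true variance 2(1 − 0.620) = 0.761; 1.960 × √(0.971/0.761) = 2.21; size 0.013.
- Month 12: ρ = 0.85 × 0.9¹² = 0.240; true variance 1.520; 1.960 × √(0.971/1.520) = 1.57; size 0.059.

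Month-3 power, with √(2/126) = 0.126:

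- Difference at the visit: 0.30/0.126 − 1.960 = 0.42, power 66%.
- Change, random intercept: (0.30 − 1.960 × 0.126 × √0.971) / (0.126 × √0.761) = 0.52, power 70%.
- Change, unstructured covariance: 0.30/(0.126 × √0.761) − 1.960 = 0.77, power 78%.
- Baseline-adjusted: 0.30/(0.126 × √(1 − 0.620²)) − 1.960 = 1.07, power 86%.

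**All four cases, by the same formulas.**

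| s, d | Size, month-3 change | Size, month-12 change | Size, linear slope | Power: change, random intercept | Power: change, unstructured | Power: baseline-adjusted |
|---|---|---|---|---|---|---|
| 0, 0.8 | 0.016 | 0.049 | 0.100 | 54% | 61% | 75% |
| 0, 0.9 | 0.013 | 0.059 | 0.112 | 70% | 78% | 86% |
| 0.5, 0.8 | 0.018 | 0.045 | 0.088 | 76% | 80% | 87% |
| 0.5, 0.9 | 0.016 | 0.051 | 0.094 | 87% | 91% | 94% |

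The slope column applies only if time is coded as one linear term. The difference at the visit has size 0.025 and power 66% in all four cases.

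**Sensitivity to the assumptions.**

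- Constant variance and correlation: size is exact. Simulation with correlation 0.6 gave two-sided 0.047 at month 3 and 0.050 at month 12, against 0.05.
- Correlation decaying by visit number instead of by month (0.8 to 0.6 per visit): two-sided 0.069 to 0.070 at month 3, that is about 0.035 one-sided. The direction at month 3 reverses.
- Baseline SD 0.6 of later SD: month-12 change size falls to 0.028–0.036. The difference at a visit rises to two-sided 0.062, about 0.031 one-sided.
- Unstructured covariance held two-sided 0.042 to 0.050 in every simulated scenario.

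**Baseline adjustment in general.** If b is the ratio of baseline SD to later SD, the change variance is 1 + b² − 2bρ = (1 − ρ²) + (b − ρ)². Adjustment is therefore never less precise than change, and it beats the difference at the visit (variance 1) whenever ρ ≠ 0. Its gain over a correctly sized change contrast disappears when b is near ρ. In the worked case with b = 0.6, 1 + 0.36 − 2 × 0.6 × 0.620 = 0.616 = 1 − 0.620².

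**The case against.** The sentence is condensed. It does not restrict the model to a random intercept, exclude a residual correlation structure, code time linearly, or name group-by-time as the treatment test. Covariance structure and target contrast are commonly left to an analysis plan, which is not shown here. Longitudinal follow-up is described as a way to watch symptom course, and Primary Outcome attaches the month-3 focus to the comparison of remission rates, not to these models.

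Much of this stands, and it limits the point. A reader might infer that the model's error rates are simply wrong for month-3 and later effects. The documents do not support that. The size errors need both a departure from constant correlation or variance and, when variance is constant, a change or slope contrast that the text never names. The between-group difference at a visit keeps its size under constant variance, whatever the correlation.

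A reader might also infer a slope test at about four times nominal, or a six-degree-of-freedom interaction test that has no direction to set against the stated threshold ("A one-sided *P* value of <.03 will be considered statistically significant"). Both presuppose a test that the article does not specify. Nor is the whole power gap a covariance problem: in the four cases about half to two thirds of it comes from baseline adjustment.

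What remains is not a missing detail. The article writes out the fixed effects, and baseline is not among the covariates, although the same article adjusts for it in the logistic model. The random effects it names have an ordinary reading that is restrictive over twelve months.

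**Conclusion.** The point holds in a conditional form. The plan states a working model for secondary outcomes and the supportive PNSC score that is weaker than an equally simple alternative.

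- **Power.** For an assumed 0.30 SD effect at month 3 with 126 per arm and equal variances, 66% (difference at the visit) or 54 to 87% (change contrast), against 75 to 94% with baseline adjustment. The loss of precision from leaving out baseline does not depend on the decay pattern, but its size depends on the baseline correlation and variance.
- **Size.** Under the assumed decay and equal variances, about 0.013 to 0.018 for the month-3 change contrast, 0.045 to 0.059 for the month-12 change contrast, and 0.09 to 0.11 if time is linear, against 0.025. A narrower baseline (SD ratio 0.6) brings month 12 down to 0.028–0.036. The direction at month 3 depends on the correlation structure. Under constant variance and correlation nothing is wrong with the size.

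The primary chi-square test, the sample size and the interim boundaries are not affected. The change is worth making because it is cheap and the article reports no recruitment as of April 2026. It does not correct a demonstrated error in a stated alpha or power.

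**What to change.** In Secondary Outcome Analysis, and by reference for the longitudinal PNSC score in Primary Outcome Analysis, replace the model sentence with wording such as:

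> Post-baseline scores (all scheduled visits after baseline) will be analyzed with a linear mixed model for repeated measures with categorical visit, group, group-by-visit, baseline score and baseline-by-visit as fixed effects, study center kept in the model, and an unstructured within-subject covariance. If this does not converge, a simpler structure with robust standard errors will be used. The treatment effect is the between-group difference at month 3 with its 95% CI; other visits are supportive.

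This needs no new data or patients, and Missing Value Handling already puts baseline outcome values in the imputation model. The cost is more covariance parameters (6 × 7/2 = 21 for six post-baseline visits, against 2 for a subject intercept and residual), which about 300 patients support easily, and a convergence fallback that must be stated in advance.

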#### Secondary Outcomes

##### Pittsburgh Sleep Quality Index

This scale is a widely used instrument comprising 19 self-rated items (which are scored) and 5 nonscored, other-rated items. The 19 scorable items are grouped into 7 components: subjective sleep quality, sleep latency, sleep duration, habitual sleep efficiency, sleep disturbances, use of sleeping medication, and daytime dysfunction. The global Pittsburgh Sleep Quality Index score ranges from 0 to 21, with a higher total score indicating poorer sleep quality [25]. Assessments will be conducted at baseline and at 1, 2, 3, 6, 9, and 12 months after enrollment.

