#### Missing Value Handling

Missing data will be handled according to the type and role of each variable. For missing diagnosis dates, original pathology records will be retrieved whenever possible. If the pathology report date is unavailable, the date of surgery will be used for imputation. If neither source can be obtained, the date of the patient’s first visit for ovarian cancer will be used, with the month imputed as July of that year and the day as the first day of the month. For baseline demographic and clinical characteristics, no imputation will be performed, and available data will be summarized descriptively. For safety outcomes, only observed AEs will be included in the analysis without imputation. For primary and secondary efficacy end points, missing follow-up data will be handled using multiple imputation under the missing at random assumption. The imputation model will include treatment group, baseline outcome values, and key prognostic covariates. Complete case analysis will be performed as a sensitivity analysis to assess the robustness of the primary findings.

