### Data Analysis

#### Final Analysis

Data analyses will be performed using R (version 4.5.3 or later).

This study defines 2 analysis sets: the full analysis set (FAS) and the per-protocol set. The primary efficacy analysis will be conducted based on the FAS, following the intention-to-treat principle, including all eligible participants with available baseline data. The per-protocol set will be used for sensitivity analyses to assess the robustness of the results. Demographic and baseline characteristics will be summarized using the FAS. Safety outcomes will be summarized descriptively.

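### The mixed models for the repeated scores include neither a baseline covariate nor a common baseline mean, which gives up precision in secondary and supportive contrasts by an amount the protocol does not fix

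*Protocol article*

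**What the plan says.** The Secondary Outcome Analysis section states the scope, "Linear mixed effects models will be used to analyze continuous variables with repeated measures (eg, scale scores at multiple time points", and then the terms: "The models will include group, time, and their interaction as fixed effects; individual subject IDs and study centers will be incorporated as random effects". The Primary Outcome Analysis section sends the continuous PNSC score to the same model: "longitudinal PNSC scores will be analyzed using the methods described below for repeated continuous outcomes". That section also plans a logistic model for remission, "with group as the main independent variable and baseline PNSC scores included as covariates".

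Baseline is available throughout. For the PNSC score, "longitudinal assessments will be conducted at baseline and at 1, 2, 3, 6, 9, and 12 months after enrollment to monitor symptom dynamics". For the PSQI, "Assessments will be conducted at baseline and at 1, 2, 3, 6, 9, and 12 months after enrollment", and the same schedule applies to the PHQ-9, GAD-7, Piper scale, EORTC questionnaire and TCM scale. Actigraphy and the sleep diary are taken at baseline and months 1 to 3. The full analysis set is described as "including all eligible participants with available baseline data". Baseline values also appear in the imputation model: "The imputation model will include treatment group, baseline outcome values, and key prognostic covariates".

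The article does not say whether the baseline visit is one of the response rows, and it names no month-3 contrast for the secondary scales.

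**The concern.** In a randomized trial the baseline value of an outcome is often its strongest predictor, and the arms have the same expected baseline. A longitudinal model can use both facts, through a baseline covariate or through a common baseline mean. The model described here does neither. There are two ways to read it:

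- **Change reading.** Baseline is a response row with a free mean in each arm. The group-by-time term at month 3 is then the difference in mean change from baseline.
- **Follow-up-only reading.** Only post-baseline visits are modeled. The contrast is then an unadjusted difference at follow-up, and chance baseline differences stay in that particular estimate.

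At stake are wider intervals and lower power for the continuous evidence on PNSC severity, sleep, mood, fatigue and quality of life. The effect on quality of life is a stated secondary objective.

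**Working it through.** **The plan's own figure.** The only sample-size figure concerns the binary primary endpoint. With rates of 10% and 40%, a margin of 15%, one-sided 0.025 and 80% power: (1.960+0.842)² × (0.10×0.90 + 0.40×0.60) / (0.30−0.15)² = 7.85 × 0.33 / 0.0225 ≈ 115.1, so 116 per group, and 116/0.8 = 145. This reproduces and is unaffected by the present point. No power or precision is stated for the mixed models.

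**Inputs.** From the protocol: 158 per group, one-sided 0.025. Assumed, because the protocol gives neither: rho, the correlation between baseline and month 3, and k, the baseline SD divided by the month-3 SD.

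**Variance of the month-3 contrast**, in units of 2 × (month-3 variance)/n:

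- change reading: 1 + k² − 2·k·rho, which is 2(1−rho) when k = 1
- follow-up-only reading: 1
- baseline covariate or common baseline mean: 1 − rho²

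The change reading exceeds the adjusted variance by (1 + k² − 2·k·rho) − (1 − rho²) = (k − rho)². This is never negative and is zero when k = rho. The follow-up-only reading exceeds it by rho², whatever k is.

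**Equal SDs (k = 1).** R is the adjusted variance divided by the planned variance. Power for an effect that has 80% power as planned is Φ(2.802/√R − 1.960).

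| rho | R, change | Power | R, follow-up only | Power |
|---|---|---|---|---|
| 0.3 | 0.91/1.40 = 0.65 | 94% | 0.91 | 84% |
| 0.5 | 0.75/1.00 = 0.75 | 90% | 0.75 | 90% |
| 0.7 | 0.51/0.60 = 0.85 | 86% | 0.51 | 98% |

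At rho 0.5 and 158 per arm, the standard error is √(2×1.00/158) = 0.112 SD as planned and √(2×0.75/158) = 0.097 SD adjusted, on both readings.

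**Simulation check.** Random-intercept data were simulated with 158 per arm, four visits, no center effect and 30 replicates per rho. Mean standard errors at rho 0.3 / 0.5 / 0.7 were:

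- change: 0.133 / 0.113 / 0.088
- follow-up only: 0.112 / 0.112 / 0.112
- baseline covariate and common baseline mean alike: 0.107 / 0.097 / 0.081

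**Smaller baseline SD (k < 1), change reading.** Eligibility requires a PNSC mean of at least 4, PSQI above 8, Piper above 4 and PHQ-9 above 5, and it excludes PHQ-9 or GAD-7 scores of 15 or more. These limits may make the baseline SD smaller than the month-3 SD.

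| rho | k | Planned variance | R | Power |
|---|---|---|---|---|
| 0.5 | 0.8 | 0.84 | 0.75/0.84 = 0.89 | 84% |
| 0.5 | 0.7 | 0.79 | 0.75/0.79 = 0.95 | 82% |
| 0.5 | 0.6 | 0.76 | 0.75/0.76 = 0.99 | 80.5% |
| 0.7 | 0.8 | 0.52 | 0.51/0.52 = 0.98 | 81% |
| 0.7 | 0.7 | 0.51 | 0.51/0.51 = 1.00 | 80% |
| 0.3 | 0.7 | 1.07 | 0.91/1.07 = 0.85 | 86% |
| 0.3 | 0.6 | 1.00 | 0.91/1.00 = 0.91 | 84% |

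A high rho also shrinks the gain on this reading. At k = 1 and rho 0.8, R = 0.36/0.40 = 0.90 and power is 84%.

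**The case against.** The schedule lists baseline among the assessment times and the model is for scores at multiple time points, so the change reading is the more natural one. On that reading baseline is used, as a change score. A reader might infer that baseline is ignored altogether, and the text does not support that. What is absent is a covariate or a common-mean constraint. This part of the objection stands.

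A reader might also see a contradiction with the logistic model. There is none. Month-3 remission is a single binary outcome, so baseline can enter only as a covariate, whereas a repeated-measures model can carry it as a response. The logistic model shows only that the authors name a baseline term when they intend one.

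A large, assured gain, such as 10 points of power, is equally tempting. It needs rho near 0.5 and equal SDs, and the entry thresholds make equal SDs doubtful for several scales. The EORTC questionnaire has no entry threshold, so the caveat has less force there.

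Finally, a condensed article may leave covariates and covariance structure to the full protocol or analysis plan. Had this article only named a mixed model, that would settle the matter. It lists the terms, however, and following them as listed gives one of the two contrasts above.

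**Conclusion.** The point holds as one of efficiency. The listed model omits both standard ways of exploiting baseline, and in large samples either of them is at least as precise on both readings. The size cannot be fixed from the document:

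- **Equal SDs, rho 0.3 to 0.7:** an 80% benchmark rises to about 86-94% on the change reading and 84-98% on the follow-up-only reading.
- **k about 0.6 to 0.8, rho 0.5 to 0.7, change reading:** the gain is about 0 to 4 points. It can be larger at lower rho.
- **Follow-up-only reading:** the loss does not depend on k.

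Because allocation is randomized, the contrasts are not systematically biased and type I error is not affected. Chance imbalance adds noise, and it stays unadjusted in the estimate only on the follow-up-only reading, which the article does not state. The primary remission test and its sample size are untouched. The change is worth making for the secondary scales and the supportive PNSC score, but the validity of the trial does not depend on it.

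**What to change.** In Secondary Outcome Analysis, choose one of:

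1. Model the post-baseline visits, with the baseline value of the same outcome and its interaction with visit as fixed covariates, alongside group, visit, group-by-visit and center.
2. Keep baseline as a response and constrain its mean to be equal in the two arms. The covariance should then let variances differ by visit, since a random intercept alone does not secure the full gain when k differs from 1.

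State that the month-3 group contrast from this model is the treatment effect, and apply the same model to the longitudinal PNSC score. This also settles whether baseline is a response row.

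The cost is a few lines of analysis wording, with no new data, visits or patients. The article reports no recruitment as of April 2026, so on that status the change can be prespecified. Because the full analysis set requires available baseline data, missing baseline values should rarely need handling.
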